## Abstract

**Background:**

Binge-eating disorder (BED) is characterized by recurrent episodes of loss of control over eating and is related to a higher prevalence of other mental disorders and somatic consequences associated with overweight and obesity. In community-based samples, 2–4% of women and 1–3% men are diagnosed with BED. Psychotherapeutic interventions focusing on maintenance factors of disturbed eating behavior have proven to be effective. However, treatment access is limited for a considerable number of patients with BED. A lack of specialized institutions and treatment resources, but also long distances to treatment facilities for people living in remote or rural areas are often causes of insufficient care. Internet-based guided self-help (GSH) programs have the potential to fill this gap.

**Methods:**

This project aims to develop and evaluate an Internet-based treatment for BED derived from an evidence-based manualized cognitive behavioral therapy (CBT). The primary goal is to test feasibility and suitability of the Internet-based program and to evaluate the treatment outcome in comparison to a pure and a placebo-inspired waitlist control group (i.e. reduction of binge-eating episodes and eating disorder pathology as primary outcome variables). In total, 60 women and men aged 18–70 years with a BED diagnosis will be recruited. The Internet-based GSH treatment comprises eight sessions followed by three booster sessions. The placebo-inspired waitlist control group receives weekly messages containing information increasing positive expectations regarding the treatment effects during the four-week waiting period. The pure waitlist control group receives weekly messages simply asking patients to fill in a short questionnaire.

**Discussion:**

The access to evidence-based treatments for BED might be made easier using an Internet-based GSH approach. The present study protocol presents a randomized controlled trial. As well as evaluating the suitability and efficacy of the Internet-based GSH treatment, there will also be a prelimarily investigation on the influence of positive expectations (placebo) for a therapeutic intervention on core symptoms.

**Trial registration:**

German Clinical Trials Register, DRKS00012355. Registered on 14 September 2017.

## Background

Binge-eating disorder (BED) is characterized by the experience of loss of control over eating, often accompanied by continuous weight gain, and is related to increased risk of the development of other mental disorders and somatic consequences associated with overweight and obesity [1]. While there are data about the course and outcome of eating disorders such as anorexia nervosa (AN) or bulimia nervosa (BN) in the general population, much less data are available on BED [2]. Besides elevated co-morbidity, current research highlights an increased risk of suicide even when accounting for co-morbidity [3]. In a community-based sample of 10,038 women and men in Switzerland aged 15–60 years, lifetime prevalence of any eating disorder (ED) was 3.5%. A total of 2.4% of women and 0.7% of men were diagnosed with BED, from which only 53.4% reported to have consulted a specialist due to their eating or weight regulation problems [4]. These measures are comparable with prevalence rates in other countries in Europe and somewhat lower than in the US [2, 3, 5]. in the absence of an appropriate treatment, the course of BED is often persistent (average illness duration of 5.79 years; SD = 8.45) in BED patients in Switzerland [4] and 4.3 years (range = 1–11.7 years) in a multinational study [6] and 8.1 years (SD = 1.1) in a US sample [7].

Even though BED represents a severe mental health condition, which can be treated efficaciously, treatment-seeking behavior and the access to treatment are limited. A recent study names the following essential barriers to treatment seeking of individuals suffering from BED: feelings of shame and fear; ED-related beliefs; and a lack of accessibility or availability of treatment [8]. The difficult accessibility of treatments is especially prevalent for people living in remote or rural areas [9]. The problem of insufficient mental health specialists able to provide therapies for Eds has also been recognized in Switzerland [10].

Disorder specific psychotherapy (cognitive behavioral therapy [CBT] and interpersonal psychotherapy [IPT]) have proven to be successful in reducing binge-eating symptomatology in the short and long term (e.g. [11–15]). Several studies have shown that among different BED treatment approaches (e.g. CBT and IPT) and settings (group or individual), up to 79% of the patients benefit from the therapy and show abstinence from binge-eating at the end of the active treatment [11, 16]. Maintenance of the therapy success in follow-up periods from 12 months up to five years has been proven in different studies from our group [13, 15]. The most thoroughly validated moderator for treatment success in BED is the reduction of binge-eating episodes by 65–70% within the first four treatment sessions (“rapid response”) (e.g. [13, 16]). A negative predictor of treatment success is over-evaluation of shape and weight. Also, the initial level of psychopathology seems to negatively influence treatment effects and it has been shown that therapeutic interventions are generally less successful with increasing duration of the ED [11, 16, 17]. The combination of pharmacotherapy and psychotherapy is not superior to psychotherapy alone and psychopharmacological medication in BED is still at an off-label-use level. Consequently, the spread and improvement of psychological treatments for BED is necessary [1] and Internet-based guided self-help (GSH) treatments are valuable treatment alternatives in BED therapy [1, 11, 18, 19].

The recently published NICE guidelines for the recognition and treatment of EDs strongly recommend GSH as the initial treatment provided in a stepped care approach [1]. CBT-based GSH treatments – in comparison to other BED related GSH – show the most pronounced positive outcomes [11, 18]. CBT GSH has been showed to be more effective compared to a waitlist control group, an unspecific therapy, and a weight-loss program. Abstinence rates of binge-eating in disorder-specific GSH were up to 64% with a significant reduction of psychopathology after treatment and at 12-month follow-up [20].

Modern technology, such as the Internet, has opened interesting possibilities for treatment delivery. These new approaches are advantageous since they are time- and location-independent, can be accessed anonymously, and thus might reduce feelings of shame and fear. They also require less implementation efforts and could be more cost-effective (less resources and infrastructure needed) than face-to-face interventions [21]. Several authors such as Aardoom et al. [22], Dölemeyer et al. [23], and Schlegl et al. [24] summarized the potential of technology-based interventions in comprehensive systematic reviews. Aardoom et al. [22] identified 21 studies on Internet-based treatments for EDs. Overall, they ascribed a high efficacy to these programs. Internet-based interventions appeared to be superior to waitlist conditions, e.g. in reducing ED pathology and binge-eating frequency, especially in individuals with less co-morbid disorders and in those suffering from binge-eating in contrast to restrictive ED symptomatology. Moreover, patients with BED showed better outcomes than patients with BN. In addition, the guidance of a therapist (e.g. via email) seems to increase the positive effects of Internet-based treatments [22]. Most of the investigated CBT-based GSH Internet-based programs are in English. Currently, there are only few studies on programs in German or French language with German- or French-speaking BED patients. The French-speaking program “Salut BED” has shown high acceptance and promising results in threshold and subthreshold BED patient as well as in obese BED patients. After six months of active Internet-based intervention, a significant reduction of binge-eating episodes, improved body image, higher psychological health, and better quality of life was observable after treatment and at six-month follow-up compared to a waitlist control group [25, 26]. “INTERBED” [27] is a German-speaking CBT-based program that has recently been evaluated in a multicenter randomized trial [28]. In this study, face-to-face CBT has proven higher efficacy than Internet-based GSH in reducing binge-eating episodes and ED pathology at the end of four months of treatment and at six-month follow-up. While the face-to-face treatment led to faster and more pronounced effects, the Internet-based GSH program still proved to be effective. At the 1.5-year follow-up, group differences no longer existed. Regarding quality of life, BMI, and general psychopathology, no difference between groups was found at any measurement point [28].

Alongside the advantages of Internet-based programs, there are also caveats such as dropout rates with high variances of 5–77%, whereas compliance was enhanced by pretreatment face-to-face assessments and therapists guidance through emails. These preliminary findings are of importance, as compliance was associated with better outcomes regarding the reduction of ED symptomatology [11, 22, 29, 30]. In a review, Schlegl et al. [24] found evidence for the efficacy of guided computer and Internet-based interventions, somewhat less for AN and more for patients with BN. They emphasized that further research is needed to understand the optimal level of therapist guidance in terms of frequency and quality. The question of the professional level of the guides and the efficacy of such programs also needs to be evaluated in comparison with face-to-face or blended treatments. Furthermore, research should address predictors and mediators of treatment outcomes.

The present randomized controlled trial (RCT) adds to existing data on treatment efficacy of Internet-based treatments for BED as the duration of treatment is shorter and additionally the effect of two waitlist conditions is evaluated. The first group is a pure waitlist control group (CG 1), where patients receive short weekly messages with a link to a short questionnaire to assess the number of weekly binges but no additional information during the four weeks of waiting time. The second group is a placebo-inspired control group (CG 2) that is provided with weekly messages with the aim to induce positive expectations regarding the program and to establish a therapeutic relationship with the therapist. This group is based on previous evidence from psychotherapy research referring to the effect of positive expectation on treatment adherence, therapeutic relationship, and dropout rate and treatment success [31–36]. Inspired by research on depressive disorder [37], this study will attempt to actively induce placebo in terms of positive expectation effects. To our knowledge, this is the first time this technique will be used in BED research. It will allow us to investigate the influence of positive expectations on treatment outcome in BED in more detail. The placebo inspired CG will allow rigorous examination of the presumably efficient disorder specific treatment that is applied in this study, since the specific active treatment is comparable to the unspecific placebo intervention.

Moreover, we will be able to indirectly compare the results of this Internet-based treatment to past studies of our group based on a GSH program with a book [38] and a face-to-face treatment [12, 14]. These are all based on the same CBT manual in order to develop hypotheses about moderators and mediators of treatment outcome for future studies.

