### Procedure

Altogether the active treatment phase including pre and post-diagnostic lasts approximately 11 weeks (plus four weeks in the control groups). The three follow-up sessions take place one, three, and six months after the last session of the active treatment. All exercises are an integral part of the sessions and mandatory. The patients are invited to work on the different exercises on an individual basis also between sessions.

Each patient is accompanied and guided by one of seven therapists that received a specific training in delivery of the current Internet-based treatment. All therapists are postgraduate psychologists or psychotherapists at the Center for Psychotherapy at the University of Fribourg and are continuously supervised by the study leaders (SM, AW). The therapists provide a weekly written feedback on the exercises via a communication system that is built into the GSH program. Patients can proceed to the next session after completing all parts of the current session along with the related exercises. The next session will then be unlocked for the patient. After finishing a session, patients will have to wait 7–10 days before they can proceed with the next session.

Since dropouts are a major problem in Internet-based treatments for EDs (up to 77%), our GSH program features several measures to support the compliance: a continuous personal contact to a therapist (face-to-face or telephone diagnostic assessment at the beginning of the program and messaging through the build-in communication system during the following three days after each session’s completion); a clear structure of the program (which has been shown to be beneficial in BED self-help programs) (e.g. [23]); and a conjoint scheduling. In addition, the introductory session provides patients with all necessary information to work smoothly through the program. Finally, the first two sessions include several interventions to develop and maintain sustained motivation. Altogether, this procedure aims at supporting the working alliance which has been positively related with the outcome in Internet-based treatments for BED [47].

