The therapists that accompany the patients during the GSH program will be trained to provide feedback according to standardized topics and text passages, based on a previous book and email-based BED treatment approach of the outpatient clinic of the research group [38]. These topics are then customized to the patient’s individual needs. The communication between therapists and patients via the built-in communication system will be continuously supervised by the first two authors (SM, AW). Treatment integrity of randomly selected communication (i.e. written contact between therapist and patients) will be evaluated by independent raters according to the previously applied procedures in face-to-face treatments of the group [14, 15].

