### Control groups (CG)

After having given informed consent, patients are randomly assigned to the TG (immediate start with the treatment) or either of the CGs. The waiting time in CG 1 (pure waitlist group) and CG 2 (placebo-inspired waitlist group) lasts four weeks. CG 2 will receive standardized weekly messages during their four-week waiting period. These messages include induction of positive expectations regarding program participation, a summary of the current evidence of BED treatment and benefits of such a standardized, evaluated treatment, quotes from former patients, and motivating words. This information does not contain any form of deception. The pure waitlist group will wait exclusively for four weeks. Both CGs fill in a short questionnaire to assess core BED symptomatology (i.e. binge-eating episodes) and to monitor changes in mood. After the waiting period, patients of both CGs start with the Internet-based GSH program.

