## Discussion

The present RCT evaluates a newly developed CBT-based GSH program delivered via the Internet. Next to accessibility and independence of time and location, another benefit of such a manualized program is the clear focus on the disorder-specific factors in treatment. The results of the present study will allow recommendations regarding suitabilty and efficacy of low-threshold interventions for patients suffering from BED [17].

We postulate several advantages for this clinical trial. First, the treatment duration of approximately 11 weeks (including diagnostics) is shorter than in the studies by Carrard et al. [25] (6 months) and de Zwaan et al. [27] (4 months). In our face-to-face treatment studies, a longer treatment period has been associated with a higher dropout rate of 30% [14] compared to 13% dropouts in a shorter, eight-week treatment [12]. Carrard et al. [26] reported dropout rates of 9% (2/22 participants in the Internet-based treatment group) and de Zwaan et al. [28] of 19.1% (17/89 participants in the GSH intervention). Second, we will apply an Internet-based version of our original BED treatment program [39], which has been systematically evaluated in RCTs in face-to-face group settings. This will enable us to indirectly compare the efficacy of the Internet-based BED treatment with data from previous studies [12–15]. Third, and for the first time in BED research, the present study investigates the role of interventions to increase positive expectations (placebo) regarding the upcoming treatment.

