The efficacy, usability, and adoption of the developed program will be evaluated through interviews, questionnaires, and analysis of interaction logs. In respect of psychotherapy research, the present study provides the possibility of examining the efficacy of a standardized disorder-specific treatment programm in comparison to a pure waiting period and a placebo-inspired intervention. Even if we make the rather conservative assumption that the specific intervention during active treatment is the “verum” that results in positive outcome and the “placebo” is not effective, we could nevertheless assume that the placebo-inspired CG shows advantages in terms of a faster positive development during treatment due to higher positive expectations and a more established therapeutic relationship already at the beginning of the active treatment. Such a result would refer to an “add-on effect” of a placebo-inspired waiting period or in other words of a preparation phase before a disorder-specific treatment, which would be relevant for clinical practice. The comparison of the present GSH program with established face-to-face therapy and a book-based GSH program, as well as the investigation of moderating and mediation variables, will improve the understanding of differential indications in BED treatment.

This research will also help to understand the specific interaction traits of users following an Internet-based treatment and to gather requirements for user interfaces that support their needs and reduce the risk of therapy drop-out. Another expected contribution of this research in the field of human–computer interaction is the exploration of mechanisms to adapt automatically the content or alerts of the therapy according to the patient specificities, towards user-induced adaptation [52] and personalized therapy.

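### The placebo-inspired waitlist group is only partly matched to the treatment group, so a treatment advantage over it cannot isolate a disorder-specific effect as the Background claims

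*Protocol article*

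**What the plan says.** The Background of the protocol article introduces two waitlist groups: a pure one (CG 1) and a placebo-inspired one (CG 2). The CG 2 messages are meant to "induce positive expectations regarding the program and to establish a therapeutic relationship with the therapist". The same paragraph ends by saying that CG 2 allows a rigorous examination of the disorder-specific treatment, and gives the reason: "since the specific active treatment is comparable to the unspecific placebo intervention".

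On what TG receives, the Procedure section says: "The therapists provide a weekly written feedback on the exercises via a communication system that is built into the GSH program". It describes sessions with mandatory exercises. Feedback starts from standard topics and text, and "These topics are then customized to the patient’s individual needs".

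On what CG 2 receives, the section on control groups says: "CG 2 will receive standardized weekly messages during their four-week waiting period". On content it says: "These messages include induction of positive expectations regarding program participation, a summary of the current evidence of BED treatment", followed by benefits of such treatment, former patients' quotes and encouragement. The section adds that no deception is involved and that both control groups start the programme after the wait. The section on sample and recruitment says there is no blinding.

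The Discussion describes the CG 2 component as "interventions to increase positive expectations (placebo) regarding the upcoming treatment" and says the study makes possible "examining the efficacy of a standardized disorder-specific treatment programm in comparison to a pure waiting period and a placebo-inspired intervention".

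**The concern.** A control group supports a claim about specific effects only if it supplies the unspecific ingredients to about the same degree as the active arm. The Background sentence asserts this property and rests the rigour of the examination on it. The Methods describe arms that do not have it.

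What is at stake is how a positive result is read. If TG improves more than CG 2 over the first four weeks, the Background sentence invites the conclusion that the disorder-specific content works beyond expectation and attention. A programme whose benefit came mainly from individual guidance, structured activity and being in treatment could produce the same result.

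The article itself treats some of these unmatched parts as active. The Background reports that therapist guidance seems to strengthen Internet-based treatment and that better compliance went with better outcomes. The Procedure section cites a positive relation between working alliance and outcome.

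**Working it through.** The point is one of design, so the check sets the described arms side by side and then asks what each contrast estimates.

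**1. The first four weeks, as described**

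| Feature | TG | CG 2 | Matched? |
|---|---|---|---|
| Written contact | Weekly therapist feedback | Weekly messages, so 4 in four weeks | Frequency roughly |
| Nature of contact | Responds to the patient's own exercises, customised | Standardised | No |
| Sessions and mandatory exercises | Yes | None described; a short questionnaire only | No |
| Relationship with therapist | Through the individual feedback | A stated aim of the messages | Partly |
| Expectation | About a treatment under way | Raised deliberately, about a treatment still to come | Partly |
| Knowledge of status | In treatment, unblinded | Waiting, unblinded, no deception | No |

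On frequency, the Procedure section sets 7–10 days between sessions. If each session is completed on the day it opens, sessions fall on days 0, 7, 14 and 21 at the shorter spacing, or days 0, 10 and 20 at the longer. TG patients thus receive about three to four feedbacks, against four messages in CG 2. The arms differ in the kind of contact and in the work attached to it, not in the count.

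**2. What each contrast estimates**

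Take CG 1 as the reference and assume, for simplicity, that effects add. Let S be the effect of disorder-specific content, U the total unspecific effect in TG (guidance, activity, alliance, knowing one is treated), and E the effect of the CG 2 messages.

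- TG − CG 1 = S + U
- TG − CG 2 = S + (U − E)
- CG 2 − CG 1 = E
- TG − combined controls, with 20 patients in each control group = S + U − E/2

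TG − CG 2 equals S only if E = U. The table gives no ground for that equality, since several parts of U have no counterpart in E. The three groups give two independent differences, which estimate E and the sum S + U. Neither separates S from U.

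**3. The stated contrast**

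The section on aim and research question states the four-week efficacy hypothesis as TG against both control groups combined. By the last line above, this removes only half of E, so it is less suited than TG − CG 2 to a claim about specificity. Model 2 in the section on statistical analysis compares time courses during active treatment and follow-up, when all groups receive or have received the programme. It does not separate S from U either.

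**4. Could the measurements support the claim?**

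In Table 2 patient expectancies are listed at t1 only, and the alliance measure is listed weekly during treatment, not during waiting. On that schedule, the degree to which CG 2 matched TG on expectation or alliance during the wait cannot be shown afterwards.

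**5. Sample size**

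More patients would narrow the interval around S + (U − E). They would not change what is being estimated.

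**The case against.** Several points on the other side are sound.

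- *Comparable* may loosely mean that the two can be compared. That is a fair reading, but the sentence still offers it as the reason the examination is rigorous, so the inference is too strong either way.
- CG 2 is not an empty control. It addresses weekly contact, expectation and, by intention, alliance. A reader might infer that nothing unspecific is controlled; the documents do not support that. Nor do they say that CG 2 patients have no reason to expect improvement while waiting.
- The article is open about what CG 2 is. It calls it a placebo-inspired waitlist group, states that nothing is blinded and that nobody is deceived, and its abstract calls the expectation question preliminary. This stands, and it means the Methods need no correction.
- No separate TG versus CG 2 test of specificity is stated; the stated contrast combines the controls. This limits the point to interpretation. It does not rescue the Background sentence, because the combined contrast serves that sentence less well.
- The Discussion makes no claim of comparability or rigour. A reader might infer that it repeats the Background sentence, but it says only that efficacy can be examined against waiting and against a placebo-inspired intervention, which is close to what the design delivers.
- A reader might also infer an inflated false-positive rate. That does not follow. If unspecific effects alone made TG do better than CG 2, rejecting equality of the two arms would be correct; only the attribution to specific content would be wrong. The documents offer no size for such effects, so no rate can be given.

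**Conclusion.** The concern holds as a limit on inference. The Background claims a property that the arms described in the Methods lack: CG 2 matches TG in frequency of contact and partly in expectation and alliance, but not in sessions, exercises, responsive individual guidance or the knowledge of being treated now. A TG advantage over CG 2, and still more over the combined controls, is evidence for the guided programme as a whole. It is not evidence for disorder-specific content over unspecific effects.

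No numerical size is attached, because none can be derived from the documents. The conclusion rests on the article's description being complete as to what CG 2 receives while waiting; it would weaken if the full protocol gave CG 2 individual, responsive contact. The additive notation is only for illustration. Randomisation, outcomes, sample size and the stated tests are unaffected.

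**What to change.** 1. **Background:** replace the closing sentence of the paragraph on the two waitlist groups with the contrast the design delivers, namely the guided programme as a whole versus waiting with standardised expectation messages.
2. **Same place:** state that no conclusion on specific versus unspecific effects will be drawn from TG versus CG 2 or from TG versus the combined controls, and that the effect of the expectation messages is assessed by CG 2 versus CG 1.
3. **Discussion:** add a short matching clarification where the *verum* and *placebo* terms are used. Nothing needs deleting there.

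The cost is a slightly less favourable claim. Nothing in the conduct of the trial changes.
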